**Fig. 3 Fig3:**
[figure not shown]
Spikes of functional electrical stimulation (FES) are visible in electromyography (EMG). X axis: 100 frames per second (100 Hz). Figure from the authors

Patients need time to get used to the electrical stimulation. Therefore, it is advised to gradually increase the stimulus intensity and the wearing time in the first four weeks: at the start, regular breaks from the stimulation are advised every hour. This can be done by turning the device off, or sitting still, because the device won’t stimulate without movement. The use of FES can be gradually increased to 6–8 h a day. The stimulus intensity of the WalkAide device can be turned up from zero to eight (maximum 121–200 mA depending on the resistance. The resistance mainly depends on the condition of the electrodes: new, clean electrodes have lower resistance and maximum stimulus of 200 mA.) (Fig. 4). At the set-up meeting, the effective stimulus intensity, i.e. the intensity that elicits a visible muscle contraction, will be determined, both in standing and walking condition. The patient decides on the intensity that is comfortable for this moment. The therapists explains the patient to increase the intensity in the coming days to weeks if necessary. Further explanation on the device, including side effects such as skin irritation, are provided, together with the device manual and spare batteries (AA batteries).5.Follow-up

**Fig. 4 Fig4:**
[figure not shown]
Buttons on the WalkAide device. Image:© 2020 Innovative Neurotronics, Inc., All rights Reserved. Usage in paper allowed

A check-up appointment will be scheduled 2 weeks after the initial set-up. Patient and parents are asked about their positive and negative experiences. Device positioning by the patient or parents will be verified, the skin is checked for irritations and the stimulus intensity is reviewed.

#### Wash-out phase

The FES phase and the conventional treatment phase will be separated by a six-week wash-out phase, because FES therapy could have therapeutic (i.e. still present without wearing the device) effects that last for a few weeks, such as an increased muscle volume [22]. However, muscle volume is not an outcome measure in this protocol. Based on previous findings, we conclude that after six weeks without FES, no remaining effects on ankle kinematics and spatiotemporal parameters should be expected and therefore our (primary and secondary) outcome measures can reliably be measured after six weeks [22, 23]. Patients can apply their conventional treatment in the wash-out phase, since AFOs/adapted shoes are not expected to cause long-lasting therapeutic changes in patients who use them for years, and it is not ethically responsible to withhold a patient a walking-aid for six weeks.

#### Conventional treatment

The conventional treatment consists of the treatment that the patient currently receives. For most patients this will consist of:AFO and/oradapted shoes and/orphysiotherapy

Patients not wearing an AFO for some reason, are also eligible to participate in the study.

Since this study compares FES treatment with conventional treatment, which is mostly AFO treatment, information about the AFO is needed. Therefore, type of AFO (static or dynamic) will be registered and the shank-to-vertical angle (SVA) will be calculated. The SVA is a parameter of the tuning of the AFO-footwear combination and should be calculated in midstance [24]. The line from the lateral epicondyle (knee joint center in sagittal plane) to the lateral malleolus is used as the shank for the calculation of the angle with the vertical [25]. According to the literature, the SVA should be between 7° and 15° in midstance, ideally 10°-12°, to align the ground reaction force to the joint rotation center.

### Outcome measures

Outcomes are grouped into the domains of the International Classification of Functioning and Health: A) Participation, B) Activities and C) Body functions & structures [7]. Fig. 5 gives an overview of the different outcome measures per domain.

**Fig. 5 Fig5:**
[figure not shown]
The outcome measures organized in the ICF model. Abbreviations: GAS: Goal Attainment Scale; CPQoL: Cerebral Palsy Quality of Life Questionnaire. Figure from the authors

### Primary objective: outcome measures in the domains of activities and participation (domains A and B)

#### Goal attainment scale (domain A and B)

The Goal Attainment Scale (GAS) is an individual outcome measure that can both describe effects per person and in groups [26]. It measures the achievement of individual, relevant goals on a 6-point scale (− 3; deterioration, till + 2; way more than the goal) [27]. The GAS is reported to be more sensitive to change than standardized functional measures [18]. Using this instrument as the main outcome measure, we want to create evidence at the level of participation and/or activities. Together with the patient, two individual goals will be prospectively defined: one aiming at the walking distance and the other one at anything that can be reflective of the FES treatment. The goals will be elaborated according to the GAS guidelines: the goal should be specific, measurable, acceptable, realistic and time-bound (SMART). The different scores (− 3 till + 2) should be clearly defined. The GAS set up and assessment will be done by a physiotherapist (SF) with previous experience regarding GAS, including training. Table 2 shows an example of the Goal Attainment Scale. The reported kappa coefficients for interrater reliability range from 0.64 to 0.89, depending on the agreements and the amount of experience with GAS [28]. For further details, we refer to previous extensive descriptions [18, 29–31]. The relevant question on this level is: *Does FES influence the achievement of individual goals in the domain of activities and participation?*

**Table 2 Tab2:** Example of the goal attainment scale

Goal Attainment Scaling (GAS)	
Definition	
Setting	John is a boy of 15 years old. Because of cerebral palsy, walking is a bit more difficult for him than for most people. Especially during day trips, for example to the zoo or a theme park, he gets really tired and he is not happy with the way he walks.
Measuring method	John will score his physical performance and stamina during a day trip, on a scale from 0 to 10: 0 means ‘very bad’ and 10 means ‘perfect’.
Assignment	John, pay attention to your physical feelings and walking performance during a daytrip.
GAS levels	
−3 deterioration	Score 3: even worse: John is really sad about his stamina and walking performance and he actually can’t fulfil daytrips in a nice way, because he needs so many breaks.
−2 baseline situation	Score 4: quite bad: John is really not happy about his stamina and walking performance. He feels really tired during the day trip and needs a lot of breaks.
−1 less than the goal	Score 5: still not sufficient: John is not happy about his stamina and walking performance, but he feels a bit less tired during the day trip. He still needs regular breaks.
0 goal	Score 6: sufficient: John feels okay about his stamina and walking performance; he feels less tired during the day trip and needs less breaks.
+ 1 more than the goal	Score 7: more than sufficient: John feels a bit happy about his stamina and walking performance: he feels less tired during the day trip and needs less breaks. He can enjoy the day more.
+ 2 way more than the goal	Score 8: more than sufficient: John feels happy about his stamina and walking performance: he feels only a bit tired during the day trip. He would like to have more day trips.

#### CPQoL questionnaire - participation (domain A)

The Cerebral Palsy Quality of Life (CPQoL) Questionnaire will be used for the assessment of participation. This validated questionnaire is about an individual’s perception of their wellbeing across various domains of life. This questionnaire has good test characteristics: internal consistency (measured as Cronbach’s α) ranges from 0.74 to 0.92 for primary caregivers and from 0.80 to 0.90 for child self-report. Test-retest reliability (measured as intra-class correlation coefficient) ranges from 0.76 to 0.89 [32]. Several CPQoL versions exist: for primary caregivers of children aged 4–12 years, for children aged 9–12 year and for teenagers aged 13–18 year. The questionnaires consist of 53 to 72 questions, scored on a 9-point ordinal scale, ranging from 1; very unhappy, to 9; very happy. Dutch versions will be used. The CPQoL question ‘How do you feel about your ability to dress yourself?’ will be used for the tertiary objective. The relevant question on this level is: *Does FES influence participation as measured by the CPQoL?*

### Secondary objective – outcome measures in the domains of body functions & - structures and activities (domain B and C)

#### Walking distance (domain B)

The six-minute walk test is a common test for functional ability: it measures the distance one can walk (without running) in six minutes. Reference values have been described for spastic cerebral palsy patients and the test-retest reliability has been established [33, 34]. Although the six-minute walk test is a laboratory test, it probably reflects the walking distance in daily life. The six-minute walk test will be performed according to the guidelines [35] on a 30 m course in a hospital hallway with walking-aid. Besides the six-minute walk test, the Functional Mobility Scale (FMS) will be applied. The FMS measures the (in)dependence in walking for several distances (5, 50 and 500 m) on a 6-point ordinal scale, ranging from 1; wheelchair bound, to 6; independent on all surfaces. The interrater reliability measured as the ICC is 0.94–0.95 for the different distances [36]. The relevant questions on this level are: 1) *Does FES change the six-minute walk distance? 2) Does FES change the FMS score?*

#### Physical activity (domain B)

Physical activity is a determinant of general health. Measuring physical activity can objectively and reliably be done using acceleration-based activity monitors. The ActivPAL3 micro (PAL Technologies Ltd., Glasgow, UK) is a small activity monitor that can be attached to the upper leg in a waterproof manner, and is capable of continuous measuring for more than seven days. It has been validated in cerebral palsy patients and the agreement with video-based analysis is 97–106% [37, 38]. In this study, all participants will wear the ActivPAL for seven complete days at time point 1, 2 and 4. The device will be attached to the not-affected upper leg in a waterproof way by the researcher to stay for seven days. Seven days are measured to make sure week- and weekend days are included, as these days might show different patterns. Sitting/lying time, upright time, stepping time, and steps taken will be collected to get insight in the physical activity of the study population and to evaluate whether FES therapy makes a change in physical activity. For these data, the algorithm of the PAL software will be used. A comparable activity monitor that is developed locally, the MOX Activity Logger (MOX; Maastricht Instruments, Maastricht, The Netherlands) will be added, to provide raw acceleration data [39]. The activity monitors will be placed on the thigh of the less affected leg, vertically above each other. The relevant question on this level is: *Does FES change physical activity in daily life?*

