## Methods

### Study design

The design of the study is a randomized crossover trial, consisting of a FES phase and a conventional therapy (mostly AFO) phase. It will be conducted at the Maastricht University Medical Center (MUMC+) in Maastricht, the Netherlands. The Medical Ethical Committee of the MUMC+ approved the study (METC azM/UM, study number 172033/NL63250.068.17). Figure 1 shows the flow chart for participants and the timing of the measurements. Four measurements will take place in total, at the start and end of every phase. Participants will take part in the study for 30 weeks. Patient recruitment and measurements will take place between August 2018 and August 2021.

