### Secondary outcomes

To assess the effect of FES and AFO treatment on gait over time, linear mixed-effects models will be performed, with gait analysis parameters as dependent variable and ‘walking aid’ (AFO, without AFO, FES, without FES) and ‘time’ [1 or 2] as fixed factors, and an interaction term ‘walking aid * time’ if applicable and a random intercept for subjects. A p-value of 0.05 is considered to be statistically significant in this analysis and Bonferroni correction for multiple comparisons is applied. Boxplot graphs will be made, showing the mean and standard deviation, as well as the individual data. This concerns the parameters: ankle dorsiflexion (in mid-swing and at initial contact), foot progression angle, foot clearance and push-off kinetics.

Nonparametric testing is expected to be appropriate for data with a source other than gait analysis, because of the lower number of observations (one measurement per time, instead of a mean of multiple measurements). This applies to the following parameters: dynamometry force, ankle range of motions based on physical examination, questionnaires (frequency of falling and toe drag, CPQoL, EQ5D-Y), physical activity and 6MWT distance. The Wilcoxon matched-pairs (signed ranks) test will be applied on the change-scores.

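### Physical activity is assigned to a matched-pairs test on change-scores but is not recorded at the start of the second phase; the 6MWT change-score depends on an aid condition that is not stated

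*Protocol article*

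**What the plan says.** Three sections of the protocol article bear on this.

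- **Study design** sets the visits: "Four measurements will take place in total, at the start and end of every phase". It adds: "Participants will take part in the study for 30 weeks".
- **Physical activity (domain B)** sets the recording: "all participants will wear the ActivPAL for seven complete days at time point 1, 2 and 4". The data are meant for more than description; one stated aim is "to evaluate whether FES therapy makes a change in physical activity".
- **Statistics, Secondary outcomes** names the outcomes handled non-parametrically, including "questionnaires (frequency of falling and toe drag, CPQoL, EQ5D-Y), physical activity and 6MWT distance", and gives one rule for them: "The Wilcoxon matched-pairs (signed ranks) test will be applied on the change-scores". The change-score is not defined.

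The 6MWT is on the same list. **Walking distance (domain B)** has it done "on a 30 m course in a hospital hallway with walking-aid" and asks whether FES alters the distance. It does not say which aid is worn when the test is done at the start of the FES phase.

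**The concern.** In a crossover with a start and an end visit in each phase, the natural change-score is end minus start within the phase, paired between phases. Physical activity has no start value in the second phase, so the test named for it has nothing to pair. An undefined change-score also leaves the definition open to choice after the results are known.

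For the 6MWT the question is what the change-score measures. FES is offered as a dynamic orthosis, so much of its benefit may appear as soon as it is switched on. If the phase-start test is already done with FES on, subtracting that test takes the immediate benefit out. What remains is habituation or training, which is a narrower question than whether FES changes the distance walked.

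**Working it through.** **1. Which visit is time point 3?** The phases last 12 weeks each with a six-week wash-out between: 12 + 6 + 12 = 30 weeks, which reproduces the stated duration. Four visits at phase starts and ends then give T1 and T2 for phase 1, and T3 and T4 for phase 2.

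**2. Which activity change-scores exist?** Recording is at T1, T2 and T4.

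- Phase 1 change, T2 − T1: available.
- Phase 2 change, T4 − T3: not available for anyone.
- Arm A (conventional first) therefore lacks the FES change, and arm B (FES first) lacks the conventional change.
- Matched pairs of within-phase changes: 0 of 22 planned completers (22 is from Sample size calculation).

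**3. The alternative reading: T1 as baseline for both phases.** (T2 − T1) − (T4 − T1) = T2 − T4. T1 cancels in every participant. The test can be run, but it is an end-of-phase comparison.

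**4. The 6MWT.** Let the expected distance be 0 with the conventional aid, let D be the immediate device effect and T the training effect over the FES phase. With no period or carry-over effect, the FES-minus-conventional contrast is:

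- change-score, FES worn at start and end of the FES phase: (D + T) − D − 0 = T
- change-score, usual aid at the start and FES at the end: (D + T) − 0 − 0 = D + T
- end-of-phase values: (D + T) − 0 = D + T

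The documents give no effect sizes or variances for this outcome, so the following is illustration only. Assumptions: n = 22, between-subject SD 0.8, within-subject SD 0.6, 3000 simulated trials, two-sided 5% Wilcoxon signed-rank test. Cells show expected contrast and rejection rate.

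| D, T (assumed) | Change, FES on at both ends | Change, usual aid at start | End-of-phase |
|---|---|---|---|
| 0.6, 0 | 0.0; 5% | 0.6; 56% | 0.6; 86% |
| 0.6, 0.2 | 0.2; 11% | 0.8; 82% | 0.8; 98% |
| 0, 0.6 | 0.6; 57% | 0.6; 58% | 0.6; 87% |

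The loss of D in the first column is algebra and does not depend on the assumed values. The rejection rates do depend on them.

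**5. Is FES on at the phase-start test?** For gait analysis the mixed model crosses the walking-aid factor, which includes FES, with time 1 or 2. That suggests FES is worn at both ends of the FES phase. For the 6MWT nothing is stated. Procedure FES set-up places the set-up meeting at the start of the phase without ordering it against the measurement.

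**The case against.** The best defence is that the change-score is undefined and its exact form may stand in an analysis plan that is not shown. A common T1 baseline is plausible: participants enter on their usual aid and may use it in the wash-out, so T1 and T3 would both be conventional-aid states. On that reading every completer has both scores. This stands in part: the data do support a paired comparison. It does not remove the mismatch, because the article itself states both the schedule and the test, and they fit only on a reading in which the baseline drops out.

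On the 6MWT, the objection that the starting aid is inferred from a different outcome is also fair. The point is conditional and is put that way.

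A reader might infer more than the documents support:

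- **That the activity question cannot be answered.** T2 and T4 still give a within-patient contrast.
- **That the device effect cancels for every outcome on the list.** Randomization and blinding tells patients to take the aid off before seeing the physiotherapist, so the physical-examination measures have no immediate device effect to lose. The questionnaires are not evidently affected either. Within-phase change is a legitimate target for therapeutic effects.
- **That carry-over inflates the FES contrast.** The Wash-out phase section grants that "FES therapy could have therapeutic (i.e. still present without wearing the device) effects that last for a few weeks". A gain present at T3 lowers the conventional change only if it fades between T3 and T4, and only in the FES-first arm; an equal gain at both visits cancels. That section also argues that no effects on ankle kinematics or spatiotemporal parameters should remain after six weeks.
- **That change-scores double the variance, as if 22 patients became 11.** This needs equal correlation between all visits, which the documents do not give, and 22 was derived for the primary outcome. The gap between the last two columns of the table rests on the same assumption.

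**Conclusion.** The schedule and the test for physical activity do not fit together. On the within-phase reading the stated test has 0 usable pairs. On the common-baseline reading it reduces exactly to T2 against T4. This rests only on the stated visit schedule and needs no assumption about effect sizes.

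For the 6MWT, the loss of the immediate device effect follows if FES is worn at the phase-start test. The gait model points that way for gait analysis, but the article does not establish it for the 6MWT.

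Both are secondary outcomes, and the primary Goal Attainment Scale analysis is untouched. One further assumption underlies any T2 and T4 activity contrast: that each monitor week falls inside the phase it represents. The article does not say whether those seven days precede or follow the visit.

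**What to change.** Reconcile Physical activity (domain B) with Statistics, Secondary outcomes:

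1. Take physical activity off the change-score list. Compare end-of-phase values, FES versus conventional (T2 and T4), within patient and accounting for period. This could be a mixed model with treatment and period, or a rank-sum test of T2 − T4 between the two sequence arms. State that the monitor week lies within the phase.
2. For the 6MWT, state which aid is worn at the start of each phase. Make the end-of-phase FES versus conventional contrast the main analysis. Use a phase-start value only as a covariate, and only where it was taken before FES was switched on.
3. For the outcomes that stay on the list, define the change-score in one sentence.

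The cost is analysis wording, with no new measurement. There are two small downsides. Within-phase change becomes descriptive for these two outcomes. An FES gain lasting to T4 in the FES-first arm would raise the conventional value there and bias the contrast toward no difference.

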#### Falling and toe drag (domain B)

Frequency of falling and toe drag will be collected by a 5-point ordinal scale questionnaire, validated by Pool et al. [23] Possible answers are never/sometimes/a few times a week/a few times a day/always, separately for toe drag and falling. Furthermore, a measurement for gait stability will be incorporated in the gait analysis (see below). The relevant question on this level is: *Does FES influence the frequency of falling and toe drag?*

#### Gait analysis parameters (domain B and C)

Gait analysis is performed at the ‘Computer Assisted Rehabilitation Environment’ (CAREN, MOTEK Medical, Amsterdam, Netherlands). Spatiotemporal characteristics, kinematics, kinetics, muscle activation patterns and fulfilled time of a fatigue protocol and fatigue score will be collected.

##### Equipment

The CAREN system consists of an instrumented dual-belt treadmill embedded in a mobile platform with a force plate underneath each belt and a motion-capture system based on reflective markers and 12 infrared 3D-cameras (100 Hz, 12 Bonita cameras, Vicon Nexus, Oxford, UK). A 3D virtual reality environment can be projected on a 180° cylindrical screen and three 2D video cameras are also included. The Human Body Model 2 lower limb with trunk kinematic model (HBM 2 lower limb with trunk, 26 markers, appendix A [40]) is used. Furthermore, a 16 channel surface electromyography (sEMG) system (Delsys Trigno) is used to measure muscle activity in both legs: 1. rectus femoris; 2. vastus lateralis; 3. semitendinosus; 4. biceps femoris; 5. gastrocnemius medialis; 6. soleus; 7. tibialis anterior and 8. peroneus longus. EMG sensors are placed according to the SENIAM guidelines (appendix B) [41]. All hardware is integrated in D-flow software (MOTEK Medical, Amsterdam, Netherlands).

##### Procedure

Marker placement according to the HBM2 lower limb model with trunk is done by an experienced team [40]. For the kinematic model, functional calibration of the hip as described by Camomilla [42] is applied if the patient is able to perform the movements of the ‘star arc’: swinging the leg forward, oblique sideward, sideward and to the back, and finally swinging the leg in half a circle (flexion of 30°, half circumduction to extension of 30°, neutral position). These movements are performed in the hip and the knee is extended as much as possible. Functional calibration of the knee is applied performing a flexion-extension movement five times on each side.

Gait analysis is performed with and without the walking-aid (AFO or FES). At the first measurement, the comfortable walking speed is determined (with aid), by gradually increasing the speed of the treadmill with 0.01 m/s per second, starting at 0.5 m/s. The participant is asked three times to give a sign at the comfortable speed. The mean of the results is used for all gait analyses. For five conditions, 250 steps (125 gait cycles) are measured:Comfortable walking speed with walking aidFast (130% of comfortable) walking speed with walking aidComfortable walking speed without walking aidFast (130% of comfortable) walking speed without walking aidComfortable walking speed after fatigue protocol, with walking aid

Fatigue protocol: after condition 4 and a short break, the ‘fatigue protocol’ starts: the speed and incline of the treadmill gradually increase and the patient is asked to walk as long as possible wearing his/her walking aid (Table 3 shows the details). If the patient says to be really tired, the protocol is stopped: the treadmill returns to a flat position and the comfortable walking speed and the last 250 steps are measured. The patient is asked to give a score (0–10) on the children’s OMNI scale of perceived exertion for his degree of fatigue.(Appendix C, [43, 44]) The fatigue protocol is performed to investigate the influence of fatigue caused by walking on the gait pattern.

**Table 3 Tab3:** Details of the fatigue protocol

Stage	Time (minutes)	% walking speed of the comfortable speed	Incline (°)	Incline (%)
1	3 (0–2:59)	70%	2	3,5
2	3 (3–5:59)	85%	4	7
3	3 (6–8:59)	100%	6	10,5
4	3 (9–11:59)	115%	8	14
5	3 (12–14:59)	135%	10	17,6
6	3 (15–17:59)	140%	12	21,3
7	3 (18–20:59)	150%	12	21,3

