### Objectives

Based on our previous systematic review [15], the overall hypothesis of the present study is that FES of the ankle dorsiflexors is an alternative to AFOs in daily life for some of the patients with CP. The primary objective is to show whether FES of the ankle dorsiflexors improves activities and participation of patients with unilateral spastic CP in daily life, measured with the Goal Attainment Scale (GAS) [18]. The secondary objective is to prove whether FES is effective at the level of body functions and structures, and activities (mainly measured with gait analysis and physical examination) and the tertiary objective is to collect relevant information on acceptability, characteristics for patient selection and cost-effectiveness to decide on implementation of FES in clinical practice. We hypothesize that the proportion of goal achievement (GAS scores) in the FES phase will be 30% higher than in the conventional phase and that FES is effective in improving ankle dorsiflexion by at least 5° during walking. Regarding characteristics for patient selection, we hypothesize that FES is effective in patients with a relatively flexible ankle joint and those who are relatively physically active, because the FES stimulation is only active during walking.

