#### Kinetics

Force plate data and kinematic data will be synchronized. For the ankle, the moment (dorsiflexion/plantarflexion) and power (generation/absorption) will be calculated over the gait cycle. The relevant question on this level is: *Does FES change ankle plantarflexion force at push-off during gait, compared to AFO or no walking aid?*

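### As listed, gait is recorded with the aid before it is recorded without it, so the with-versus-without contrasts in the secondary gait analysis are confounded with position in the session

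*Protocol article*

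**What the plan says.** In the protocol article, the Procedure section under Gait analysis parameters has each session recorded both with and without the walking aid: "For five conditions, 250 steps (125 gait cycles) are measured". The list runs: 1, comfortable speed with aid; 2, fast (130% of comfortable) with aid; 3, comfortable without aid; 4, fast without aid; 5, comfortable with aid after the fatigue protocol. The next sentence ties the numbering to the running of the session: "after condition 4 and a short break, the ‘fatigue protocol’ starts". No randomised or alternating order is mentioned.

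The Secondary outcomes section under Statistics analyses the gait parameters with a linear mixed model. Its fixed factors are walking aid, with four levels (AFO, without AFO, FES, without FES), and time, with their interaction if applicable and a random intercept per child. It names no term for order or position.

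The Kinetics section asks about push-off with FES "compared to AFO or no walking aid". The Objectives section sets the hypothesis that "FES is effective in improving ankle dorsiflexion by at least 5° during walking".

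**The concern.** With versus without the aid is a formal contrast in the gait model, and the push-off question names no walking aid as one of its two comparators. If the unaided recordings always come second, the contrast measures the aid plus whatever changes over the session. Tiring would lower the unaided values and flatter the aid. Getting used to the treadmill would raise them and hide a benefit. Because the order repeats at every visit, more children or visits would not shrink the error.

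The protocol treats walking fatigue as worth studying: "The fatigue protocol is performed to investigate the influence of fatigue caused by walking on the gait pattern". The unaided runs also follow different exposures in the two phases: stimulated steps in the FES phase, usually braced steps in the AFO phase. The drift need not be equal in the two.

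**Working it through.** The plan gives no figure for an order effect, so there is none to reproduce. The check is whether aid and position can be told apart, and how drift enters the estimate.

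**Inputs from the protocol article:** five conditions of 250 steps in the listed order; fatigue protocol after condition 4; four walking-aid levels and no order term; 5° dorsiflexion target (Objectives); earlier FES effects of 2° to 12° at initial contact compared with no FES (Treatment, in the Background); at least 22 completers (Sample size calculation). One comfortable speed, set with the aid at the first measurement, is used throughout, so speed adds no further confounding.

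**Exposure before the first unaided recording:** 2 × 250 = 500 steps, half of them at 130% speed. At an assumed cadence of 90 to 130 steps per minute this takes 500/130 = 3.8 to 500/90 = 5.6 minutes.

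**Identifiability, conditions 1 to 4.** Let a = 1 with the aid and 0 without, f = 1 for fast, and h = 1 for the second half.

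| Condition | a | f | h | linear position p |
|---|---|---|---|---|
| 1 | 1 | 0 | 0 | 0 |
| 2 | 1 | 1 | 0 | 1 |
| 3 | 0 | 0 | 1 | 2 |
| 4 | 0 | 1 | 1 | 3 |

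Here h = 1 − a and p = 2(1 − a) + f, both exactly. A design with intercept, aid, speed and position has rank 3 of 4 under either coding. If half the children walk 3-4-1-2, the rank is 4 of 4.

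**Condition 5.** It has a = 1, f = 0, p = 4, while 2(1 − a) + f = 0. The identity breaks, so a straight-line drift over all five recordings could formally be fitted. That line would have to run through a protocol rising to a 12° incline and 150% of comfortable speed over up to 21 minutes. If condition 5 is instead given its own block effect, h = 1 − a still holds in the other four and aid stays aliased.

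**Bias.** Let τ be the aid effect and δ the shift in the second block.
- Fixed order: with minus without = τ − δ. A fall of 1° (δ = −1) gives τ + 1; a gain of 1° gives τ − 1.
- Counterbalanced, equal shift: ½(τ − δ) + ½(τ + δ) = τ.
- Counterbalanced, shift δ₁ when unaided walking comes second and δ₂ when aided walking comes second: τ + (δ₂ − δ₁)/2. Unequal carry-over is not removed.
- FES on/off effect minus AFO on/off effect, fixed order: (τ_FES − τ_AFO) − (δ_FES − δ_AFO). Drift cancels only if it is equal in the two phases.

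**Scale, assumed drift of 1° to 2°:** 1/5 = 20% and 2/5 = 40% of the target. Against the reported 2° to 12°, it is 1/2 = 50% to 2/2 = 100% of the low end and 1/12 = 8% to 2/12 = 17% of the high end.

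**Illustration** (simulation; 22 children, assumed SD of 3° per condition mean, no true aid effect, nominal 5%, no Bonferroni correction): in fixed order, drifts of 0°, 1° and 2° gave false-positive rates of about 5%, 19% and 56%. Counterbalanced, with equal shift, bias was 0.0° and the rates were 3% to 5%.

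**The case against.** **The order is inferred.** The list is introduced as a set of conditions, and only what precedes the fatigue protocol is tied to a number; nowhere is it said that every child at every visit follows it. A condensed article may also leave session order to the full protocol. This stands as a caution. But the sentence about condition 4 uses the list as a running order, and it would be untrue for children walking 3-4-1-2.

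**Fatigue may be slight.** A reader might infer that the protocol expects walking to alter gait within these recordings. It says only that this will be investigated, and it uses steep inclines and higher speeds to provoke it. Conditions 1 and 2 are short for children in GMFCS I or II who must be able to walk 15 minutes to enter. This stands: the size of the drift is unknown, and since habituation works the other way, so is its sign.

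**The 5° target.** A reader might take it as a with-versus-without-FES target because the earlier effects are reported that way. The Objectives section names no comparator, so 5° serves here only as a yardstick.

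**Condition 5 repeats the aided state.** It is therefore too strong to say that no analysis of the recorded data could inform on drift: comparing 1 with 5 gauges change after heavy walking. It does not isolate drift between blocks 1 and 2, and the planned model does not use it for that.

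**The main comparisons are untouched.** This stands in full. The Goal Attainment Scale does not depend on the gait session, and FES worn versus AFO worn is compared at the same position.

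**Conclusion.** The point holds for the within-session with-versus-without contrasts on dorsiflexion, foot clearance and push-off, and for nothing beyond them. On the plain reading of the list, aid on or off is confounded with session position in conditions 1 to 4, and the stated mixed model cannot separate them. Whatever drift exists enters one for one. Neither its size nor its direction can be taken from the documents; the 20% to 40% of target rests on an assumed 1° to 2°, and the false-positive rates rest on that and an assumed SD. The documents do not support the conclusion that the benefit of FES is overstated, nor that the trial's primary result or its FES-versus-AFO comparison is compromised. This is a cheap improvement to a secondary analysis.

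**What to change.** Counterbalance the aid and no-aid blocks: within each arm, assign half the children at inclusion to walk conditions 3 and 4 before 1 and 2. Keep each child's order the same at all four visits, so that FES and AFO are still compared within child at matched positions. Keep the fatigue protocol last. Add block order to the gait model, coded as whether a recording fell in the first or second block of its session. If carry-over after stimulated and braced walking may differ, add its interaction with walking aid. With about 11 children per order (22/2) that interaction will be imprecise, and counterbalancing alone does not remove unequal carry-over.

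The cost is an assignment list, one or two model terms and slightly more complex sessions, with no extra recordings. At visit 1 the aid is already worn to set the speed, so the reversed order (on, off, on) needs two aid changes, as now. At later visits it needs one (off, on) instead of two.

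Measurements were scheduled from August 2018 to August 2021 and the article appeared in January 2022, so the sessions may be complete. For any recorded in fixed order, state the confounding, present the with-versus-without contrasts as descriptive, and base inference on FES versus AFO at matched positions. If the order was in fact varied, say so and report it.
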